## Abstract

**Background:**

The treatment of mental health issues among people living with HIV (PLH) in Botswana is yet to be addressed. A recent study revealed that depressive symptoms are highly prevalent in a sample of PLH in Botswana. Based on empirical findings of a study that investigated intervention targets for PLH in Botswana, a self-help program with coaching in booklet format in the Setswana and English languages was developed, composed of cognitive behavioral techniques, coping skills interventions, and goal adjustment training. We will investigate the program for effectiveness in the treatment of depressive symptoms among PLH. Additionally, we will investigate treatment moderators and mediators. This paper describes the study protocol.

**Methods/design:**

A randomized controlled trial will be conducted to compare the booklet self-help program with coaching with an attention-only control condition, by including pre-test, post-test, and follow-up assessments. We aim to enroll 200 participants with mild to moderate depressive symptoms into the study. The self-help program contains the following main components: activation, relaxation, changing maladaptive cognitions, and the attainment of new personal goals. This content is covered over six lessons to be completed in a maximum of 8 weeks. It uses a combination of psycho-education, assignments, and exercises. The participants will work on the program 1–2 h every week for 6 weeks (maximum 8 weeks). Coaches will offer support and motivate the participants. For both groups, depressive symptoms and possible mediators will be measured three times during the intervention, and at pre-test, post-test, and follow-up.

**Discussion:**

If the intervention is found to effectively treat depressive symptoms, it will be implemented and thus help improve the psychological health of PLH in Botswana.

**Trial registration:**

Netherlands Trial Register, NTR7428. Registered on 23 August 2018.

**Electronic supplementary material:**

The online version of this article (10.1186/s13063-019-3584-0) contains supplementary material, which is available to authorized users.

## Background and objectives

In sub-Saharan Africa, the rate of new HIV infections as well as mortality due to HIV has reportedly gone down in recent years [1]. The decrease in HIV mortality and new infections can be credited to an increased access to antiretroviral therapy (ART) as well as the introduction of other HIV prevention programs such as prevention of mother-to-child transmission (PMTCT) and increased access to condoms [1]. Consequently, HIV is now considered a chronic illness [2–4], and this shift has led to increased attention to the overall management of HIV. There have been great investments in policies and medical programs that ensure easy access to ART by people living with HIV (PLH) [5]. This has been the case particularly in Botswana. The UNAIDS 2017 report [1] shows an overall increase in ART access by PLH in Botswana and sub-Saharan Africa.

While medical care has received a lot of attention, addressing the mental health care of PLH has lagged behind, despite the reported high prevalence of mental health problems among PLH. Numerous literature sources have documented that mental health issues not only put a heavy burden on PLH but are also considered as important and common barriers to treatment adherence [6, 7]. One mental health factor that has been cited as especially important in this regard is depression [8]. In sub-Saharan Africa, depression has been shown to be the leading mental illness among PLH [7, 9, 10]. Based on self-report measures for depressive symptoms, the reported prevalence rates for depressive symptoms among PLH in sub-Saharan Africa vary quite widely, between 8 and 64% [9–12]. In Botswana, one study has reported a prevalence of depressive symptoms in women living with HIV of 48% [13]. Another, more recent study has found a prevalence rate of depressive symptoms among 291 PLH in Botswana of about 43% ([name] et al., “Depressive symptoms among people living with HIV/AIDS in Botswana: a search for intervention targets for a coping-skills intervention,” submitted). Given the potential threat of depression to the health and well-being of PLH and to treatment adherence, it is critical to treat depressive symptoms among PLH. Unfortunately, no treatment programs specifically designed for PLH in Botswana exist. This is in part due to a mismatch between the demand for psychological services and the resources available [14]. Mental health services are provided by a limited number of psychologists and about 10 psychiatrists who serve the entire population of Botswana [15]. For a population of about 2 million, it can be assumed that the mental health services available do not reach everyone who needs them.

Until now, there is little evidence of effective intervention programs for depressive symptoms in PLH in sub-Saharan Africa. In Western countries, some intervention programs have effectively treated depressive symptoms in PLH [16–23]. Depressive symptoms were assessed through different self-report measures. The content of the programs, mostly employing techniques from the cognitive behavioral approach, include stress reduction techniques and the facilitation of adaptive coping skills (including changing of maladaptive cognitions and behaviors) [16, 24]. Some interventions occur face to face, individually, or in small groups; others are in self-help, online, or booklet format.

One such program with good results is the recently developed cognitive behavioral self-help program “Living positive with HIV”. This self-help program was developed based on findings from research on the predictors of psychological well-being in PLH. The self-help program is aimed at reducing depressive symptoms among PLH [19, 25]. It is available both online and in booklet format and is low cost. It consists of weekly lessons and can be provided with or without (minimal) coaching. Participants are expected to work on the program on a weekly basis. The Living positive with HIV program in booklet format was found to be significantly effective in reducing depressive symptoms among Dutch PLH, both in the short term and in the long term [19]. A recent randomized controlled trial (RCT) found the online version to also effectively reduce depressive symptoms among PLH [23]. The inclusion criteria for the Living positive with HIV program were being HIV positive, presenting with mild to moderate depressive symptoms, being aged 18 years and older, having adequate knowledge of the Dutch or English language, having Internet access and an email address, and being available for 8 weeks in order to complete the intervention [23].

It was argued that a similar self-help program might effectively reduce depressive symptoms in PLH in other countries, in this case Botswana, at low cost. To ensure that such a treatment program would be evidence based and would address the unique needs and circumstances of PLH in Botswana (and other sub-Saharan countries), an empirical study was performed that investigated the prevalence and risk factors of depressive symptoms, the needs of PLH, and the feasibility of an intervention program in a sample of 291 PLH in Botswana (the aforementioned study of [name] et al.). Participants indicated a need for help with various mental health issues such as feelings of depression, feelings of anxiety, physical tension, coping with HIV, and finding new goals in life. Several coping strategies were found to be significantly related to depressive symptoms, such as rumination, positive refocusing, refocus on planning, catastrophizing, and withdrawal. Participants indicated a preference for a program in booklet format over an online program.

Based on the empirical findings and indicated needs, a self-help program with coaching in booklet format for PLH with depressive symptoms in Botswana was developed, composed of cognitive behavioral techniques, coping skills interventions, and goal adjustment training. For our purposes, goal adjustment training refers to helping patients to find realistic goals that they want to achieve and developing a concrete action plan to attain these goals.

This program will be investigated for effectiveness in the treatment of depressive symptoms among PLH. This paper describes the study protocol. By conducting an RCT, the booklet self-help program with coaching will be compared with an attention-only control condition. In addition, we will investigate treatment moderators, to study whether the program is more beneficial to some patients than to others. We will also investigate mediators of treatment, to study which mechanisms are related to treatment outcome.

## Methods/design

### Design

To evaluate the effectiveness of an intervention recently developed for PLH in Botswana, an RCT will be performed. The trial will have two conditions: an intervention group, who will receive the self-help program with coaching for depressive symptoms, and an attention-only control group, who will receive the self-help program without coaching following completion of the follow-up measurement. Random allocation of participants to the intervention or control group will be performed using a stratified random sampling technique. The sample will be stratified according to gender and treatment center. It is important to stratify by gender to ensure approximately equal proportions of males and females in the intervention and control groups. In the study by [name] et al. that investigated intervention targets for depressive symptoms among PLH in Botswana, more females participated compared to males. Additionally, treatment centers are expected to differ with regard to the number of patients included; therefore, stratification will ensure that both the intervention and control groups in large and small treatment centers have almost the same numbers of patients in both conditions.

Random number tables will be used to allocate participants to either condition; these will be computer generated and produced by an independent researcher. Randomization will be done in permuted blocks of six. The independent researcher will enter the numbers into an Excel file which will conceal the randomization until after the participants are established in the trial. The randomization is set up such that the main researcher is unable to see treatment allocation beforehand, minimizing bias. Participants and coaches will not be blinded to allocation to conditions. Participant allocation to one of the conditions will be done after the pre-test.

The study is approved by the Health Research Development Committee of the Ministry of Health in Botswana (Ref. HPDME 13/18/1). The Standard Protocol Items: Recommendations for Interventional Trials (SPIRIT) checklist is provided as Additional file 1.

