### Participants

We will recruit about 200 participants from six HIV treatment centers in Botswana. These treatment centers were selected strategically to include the two largest referral hospitals serving the northern and southern ends of Botswana. As referral hospitals, they service PLH from different parts of the country, thus giving the study an increased likelihood of recruiting participants from various backgrounds.

Recruitment of participants will be conducted using a short initial screening during their regular visits to the HIV medical staff. Further screening will be done by the researchers. The inclusion criteria for participation in the study are as follows: being HIV positive, presenting with mild to moderate depressive symptoms (that is, a score greater than 4 and less than 20 on the Patient Health Questionnaire 9 (PHQ-9) [26], aged 18 years and older, having sufficient knowledge of the Setswana or the English language, and available for the next 8 weeks to work on the intervention. The exclusion criteria are as follows: (almost) no symptoms of depression (a score of 4 or less on the PHQ-9), presenting with severe cognitive impairments (medical staff and coaches to use their clinical judgement to determine if the patient may be presenting with severe cognitive deficits), being in the first 6 months post-HIV diagnosis, and suicidality as determined by a score of > 1 on the suicide item of the PHQ-9. Those who score within the severe depressive symptoms range (≥ 20) or suicide ideation as measured by the PHQ-9 will be referred for face-to-face psychological or psychiatric treatment or to a medical doctor at the treatment center.

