### Sample size

To determine the sample size needed for the RCT, we performed a power analysis using the 14th Edition of the Power Analysis and Sample Size Software (PASS) [27]. It was calculated that each group should consist of 64 participants (effect size = 0.50, alpha = 0.05, and power = 0.80). Similar studies have recorded a dropout rate of 15%; therefore, at least 75 participants should be allocated to each group. Taking into account the possibility of further dropout at follow-up, a total of 200 participants will be recruited for the RCT.

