### Statistical analyses

Data will be analyzed using an intention-to-treat (ITT) analysis [43]. We will use a two-tailed alpha of 0.5 for significance testing. To investigate baseline differences between conditions, we will use chi-square and analysis of variance (ANOVA) tests for categorical and continuous variables, respectively.

Differences between groups in depressive symptoms from pre-test to post-tests will be investigated using longitudinal multilevel regression analyses (LMRAs) [44]. We will adopt a two-level model where time and group will be included as fixed effects and the slopes for time and the intercept as random effects. The between-group analysis will include the pre-test, post-test, and follow-up. To investigate the long-term effects of the intervention, we will include the pre-test, post-test, and follow-up in the within-group analysis. To estimate the effects in the model, we will employ a maximum likelihood estimation type. We will also study the differences between participants who followed the intervention to the end and those who dropped out with chi-square tests and ANOVAs.

Furthermore, Cohen’s *d* will be used to calculate within- and between-group effect sizes. Effect sizes less than 0.20 are regarded as having a small effect, 0.50 a medium effect, and 0.80 a large effect [45]. We will also explore clinically significant differences for individual change in depressive symptoms. Individual change scores of 5 or more for the PHQ-9, from pre-test to post-test and follow-up, will be regarded as clinically significant [46]. The same approach will be used to examine pre-treatment versus post-treatment changes with regard to all secondary outcomes.

We will examine moderators of the treatment outcome using LMRA. We will enter potential moderators individually. Additionally, we will employ the latent difference score model for mediation analysis [47].

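### The planned primary model leaves out gender and treatment center, the two randomisation strata; adding them is a low-severity, nearly free improvement

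*Protocol article*

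**What the plan says.** The Design section of the protocol article fixes the randomisation: "The sample will be stratified according to gender and treatment center", and "Randomization will be done in permuted blocks of six". Its stated reasons are balance between the arms on gender and, because centers will differ in size, "almost the same numbers of patients in both conditions" within each center. The Participants section gives the number of centers: "We will recruit about 200 participants from six HIV treatment centers in Botswana". Gender by center thus makes 2 × 6 = 12 strata.

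The Statistical analyses section specifies the model in some detail: two levels, maximum likelihood, random intercept and random time slope, and "time and group will be included as fixed effects". Pre-test, post-test and follow-up all enter the between-group analysis. No group-by-time term is written out. Gender and center are not listed.

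Elsewhere, the Ethical precautions section names one covariate, referral to more intensive treatment, which arises after randomisation. The Assessments section lists gender among the potential moderators; the Statistical analyses section examines moderators one at a time, which does not adjust the main model.

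**The concern.** Blocked randomisation within strata makes the arms nearly equal on gender and center by design, so differences between strata contribute almost nothing to the chance variation of the treatment contrast. A model without the strata still counts those differences in its error terms. For a comparison of levels, the reported standard error then exceeds the true one: confidence intervals are wider than they need be, the actual type I error falls below the nominal rate, and some power is lost.

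The size of the loss depends on two things that the article does not settle: how strongly gender and center predict PHQ-9, and whether the treatment effect is a difference in level or a difference in change.

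**Working it through.** **Inputs.** From the Sample size section: effect size d = 0.50, alpha 0.05, power 0.80, 64 per group, 15% dropout, 75 per group, 200 in total. From Design and Participants: 12 strata, blocks of six, about 1:1 allocation. Assumed: R², the share of outcome variance explained by gender and center, taken as 5%, 10% and 20%. All figures use two-sided alpha 0.05, the value that reproduces the sample size; the Statistical analyses section prints 0.5, which is a separate matter to reconcile.

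**The plan's own figure.** A two-sample t-test with d = 0.50 and 64 per group has power 0.801, so 64 is reproduced. 64/0.85 = 75.3, in line with the stated 75. With 85 per group power is 0.90, and with 100 per group 0.94. None of this takes credit for the strata.

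**Post-test comparison.** True SE = unadjusted SE × √(1 − R²), so the unadjusted SE is too wide by the factor 1/√(1 − R²). Adjusted power is that of a t-test with effect size 0.50/√(1 − R²).

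| R² | SE too wide by | Adjusted power, 64 per group (0.801 planned) | Adjusted power, 100 per group (0.940 unadjusted) |
|---|---|---|---|
| 5% | 1/√0.95 = 1.026, 2.6% | 0.821 | 0.951 |
| 10% | 1/√0.90 = 1.054, 5.4% | 0.841 | 0.960 |
| 20% | 1/√0.80 = 1.118, 11.8% | 0.881 | 0.976 |

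Against the planned 0.801, the gain at 64 per group is 2 points at R² 5% and 4 points at 10%. That is an upper figure, because stratification already lifts the real power of the unadjusted test slightly. In the normal approximation, with z = 0.5/√(2/64) = 2.83, unadjusted power is Φ((z − 1.96)/√(1 − R²)) and adjusted power is Φ(z/√(1 − R²) − 1.96). These give 81.4% to 82.7% at R² 5% and 82.0% to 84.6% at 10%, gains of 1.3 and 2.6 points. The actual type I error without adjustment, 2(1 − Φ(1.96/√(1 − R²))), is 0.044 and 0.039.

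**Longitudinal model.** Trials were simulated with six unequal centers, 70% women, blocks of six in 12 strata, within-person correlation 0.5 and stratum effects equal at every visit (3,000 trials per setting). Random-intercept mixed models were also fitted to simulated trials with 15% and 25% dropout at post-test and follow-up (60 per setting).

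| R² | SE ratio without/with strata, group main effect | SE ratio, group-by-time | Power for group main effect at N = 200, without → with strata |
|---|---|---|---|
| 5% | 1.05 | 1.001 | 0.825 → 0.842 |
| 10% | 1.09 | 1.002 | 0.835 → 0.876 |
| 20% | 1.20 | 1.005 | 0.863 → 0.931 |

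The main-effect loss exceeds that of a single visit because averaging visits removes within-person noise and leaves the strata a larger share. With three visits and correlation 0.5, the variance of a participant's mean is (1 + 2 × 0.5)/3 = 0.667, so the share is R²/0.667 = 1.5 R². For R² 10%, 1/√(1 − 0.15) = 1.085, close to the simulated 1.09.

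For change from pre-test, stable stratum differences sit in the random intercept and cancel. Simulated type I error stays near 0.05 and power does not move.

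**When strata predict change.** Suppose the stratum effect is present at post-test only. With pre-post correlation 0.5, the change score has variance 2(1 − 0.5) = 1, so strata explain the same R² of it. The SE is again about 2.6% or 5.4% too wide; simulation gave 2.5% and 5.2%. Only terms that let stratum effects differ by visit recover this.

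**The case against.** The strongest objection is that the planned model is longitudinal and its stated aim is the difference between groups from pre-test onwards. On that reading the post-test formula describes another analysis, and adding gender and center as main effects changes the SE by 0.5% at most. This stands, with two limits. No group-by-time term is written, so a difference in level is the literal reading of the listed terms. The cancellation also needs stratum differences to be constant over visits; the PHQ-9 entry range of 5 to 19 could compress them at baseline, and the protocol itself treats gender as a possible moderator.

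Second, the document nowhere shows that gender or center is prognostic; stratification is justified by balance alone. This stands, and makes every figure conditional.

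Third, a condensed article need not list every covariate, and referral is indeed named outside the Statistical analyses section. This stands in part. Full covariate lists are often left to a fuller document, but here the levels, fixed effects, random effects and estimator are all given, and the model so described does not follow the randomisation.

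A reader might infer that the omission makes the primary test invalid, or leaves the trial underpowered. The document supports neither. Any error is conservative, and the 64 per group takes no credit for the strata, while "a total of 200 participants will be recruited for the RCT" leaves a margin above it. Nor can one say without condition that power is given away.

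**Conclusion.** The point holds as a low-severity inconsistency: randomisation is stratified by gender and center, and the model as specified contains neither. If the strata are prognostic and the effect is a level comparison at post-test, standard errors are about 2.6% too wide at an assumed R² of 5% and 5.4% at 10%. The matching power gain at 64 per group is about 2 and 4 points against the planned figure, or 1.3 and 2.6 against the unadjusted test's real power. A literal group main effect over all visits loses more, about 5% and 9% in the SE. For a pre-to-post change contrast, main effects alone gain almost nothing, and there is something to recover only if the strata predict change. All sizes rest on assumed R² values and, for the longitudinal results, on a within-person correlation of 0.5.

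**What to change.** In the Statistical analyses section, add gender (1 degree of freedom) and treatment center (5 degrees of freedom) as fixed effects in the primary longitudinal model and in the models for secondary outcomes. State which term is the treatment effect. If it is group-by-time, let gender and center interact with time as well; main effects alone would not help there. Set in advance a rule for pooling centers that recruit very few participants, since 200/12 is only about 17 per stratum on average and centers are expected to differ in size. If the factors are to stay out, say why.

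The cost is a line or two of text and 6 degrees of freedom for the main effects, plus 6 more for interactions with linear time or 12 with three categorical visits, out of about 200 participants. Both variables must be known at randomisation, so no new data are needed. According to Trial status, recruitment had not started.

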**Fig. 1 Fig1:**
[figure not shown]
Flowchart of the study design

In Botswana, the majority of patients who have been on treatment for more than a year visit the treatment center once every 6 months; therefore, the screening will be conducted over a period of approximately 6 months. Any patient who obtains a score > 0 on the PHQ-2 and who meets the inclusion criteria may be referred to the researchers. The HIV consultants will provide written information about the study to the patients and request for permission to provide the researchers with the patient’s contact information (telephone number or email). Following contact with the patients, the researchers will provide further information to the patients and conduct extensive screening for depressive symptoms using the PHQ-9 by telephone. Patients with a score within the mild (> 4) and moderate (< 20) ranges will be eligible for participation in the trial. These patients will then be invited to participate. Those who agree to participate will give consent by a text message to the researchers. Additionally, we will seek permission from patients to inform a medical doctor or general practitioner at the HIV treatment center about their participation in the study. Participants will then undergo a pre-test (T0). Thereafter, the participants will be randomly assigned to the intervention or the control (attention-only) group. The coaches will call all participants at the beginning of the intervention to assess for and stimulate their motivation. This will be accomplished through the use of motivational interviewing and general conversational techniques, providing information about the program, helping the patients plan for the lessons, and advising them to engage in a small activity to get started.

The intervention group will then receive the self-help treatment program with coaching by telephone, while the control group will only receive attention through a weekly telephone chat from a coach. The participants will work on the intervention for 6 weeks (with a maximum extension of 2 weeks). During the intervention, participants will be asked to answer standardized questions at three different times. At 8 weeks, all participants will complete the post-test (T1) and subsequently the follow-up measurement (T2) 3 months later. After the follow-up, participants in the control condition will receive the intervention.

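### One fixed, published block size of six in an open, stratified trial makes up to a quarter of allocations (about 21–22% here) deducible by anyone who tracks earlier allocations by stratum

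*Protocol article*

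**What the plan says.** All references are to the protocol article.

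- **Block size and strata (Design).** "Randomization will be done in permuted blocks of six"; "The sample will be stratified according to gender and treatment center". No ratio is written, but the stated aim that "large and small treatment centers have almost the same numbers of patients in both conditions" implies 1:1, hence three and three per block.
- **Size (Participants).** "We will recruit about 200 participants from six HIV treatment centers in Botswana".
- **Concealment (Design).** An independent researcher produces the list and enters it in "an Excel file which will conceal the randomization until after the participants are established in the trial". The section adds: "The randomization is set up such that the main researcher is unable to see treatment allocation beforehand, minimizing bias". Allocation comes after the pre-test.
- **Blinding (Design).** "Participants and coaches will not be blinded to allocation to conditions". The blinding of the researchers is not addressed.
- **Who recruits (Procedure).** After referral from the clinic, "the researchers will provide further information to the patients and conduct extensive screening for depressive symptoms using the PHQ-9 by telephone". They then invite eligible patients and conduct the pre-test (T0) by telephone, all before allocation.
- **Who sees the arms (Support from a coach).** The researchers supervise the coaches. The main researcher meets them weekly in the first month and every two weeks afterwards. Call recordings and notes are used in supervision. Calls last about 15 minutes in the intervention arm and about 5 minutes in the control arm, with different content.

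**The concern.** Concealment has two parts: nobody may look up the next assignment, and nobody may work it out from earlier ones. The Design section secures the first. The second is weak because the block size is constant and public, both stratification factors are visible before allocation, and assignments are open once made. When one arm has used its three places in a block, the rest of that block is forced.

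The people placed to make this deduction are those with influence before allocation. Supervision gives the researchers access to the arm of participants already enrolled, and the same role screens with the PHQ-9, invites, and interviews at T0. The PHQ-9 is also a primary outcome, and its pre-test value enters the between-group model described under Statistical analyses. Foreknowledge could therefore affect who enters and the recorded baseline. That is selection bias, which the Design section presents its set-up as minimizing.

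**Working it through.** The document gives no predictability figure to reproduce, so the check starts from its design inputs.

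**Inputs.** Block size 6, 1:1 (Design); strata gender × center (Design); about 200 participants and six centers (Participants). With gender at two levels there are 6 × 2 = 12 strata, 200/12 = 16.7 participants per stratum, and 16.7/6 = 2.8 blocks per stratum.

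**Step 1: certainty within one complete block.** There are C(6,3) = 20 equally likely sequences. A place is forced if one arm has already used its three.

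| Place in block | 1 | 2 | 3 | 4 | 5 | 6 |
|---|---|---|---|---|---|---|
| P(forced) | 0 | 0 | 0 | 2/20 = 0.10 | 8/20 = 0.40 | 1.00 |
| P(best guess correct) | 0.5 | 0.6 | 0.6 | 0.7 | 0.7 | 1.0 |

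Forced: (0.10 + 0.40 + 1.00)/6 = 1.5/6 = 25.0%. This agrees with the closed form 1/(m + 1) for blocks of 2m: 1/(3 + 1) = 25%. Best guess: 4.1/6 = 68.3%, against 50% by chance.

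**Step 2: unfinished last blocks.** Forced places come late in a block, so a stratum that stops mid-block loses some.

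- At 17 per stratum (two full blocks plus five places): certain = (2 × 1.5 + 0.5)/17 = 3.5/17 = 20.6%; best guess = (2 × 4.1 + 3.1)/17 = 11.3/17 = 66.5%.
- With 200 participants spread at random over 12 strata, simulation gives a mean of about 22%, with single runs between about 20% and 24%. Equal strata and two assumed uneven splits by center and gender give nearly the same mean (21.8% to 22.0%).

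**Step 3: randomly varying block sizes, same stratum size.** Simulation at 17 per stratum, with an observer who knows the set of possible sizes and the full ordered history of the stratum:

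| Blocks | Certain | Best guess correct |
|---|---|---|
| Fixed 6 | about 21% | 66.5% |
| Random 4, 6, 8 | about 2.4% | about 66% |

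Certainty falls about ninefold (20.6/2.4 = 8.6). The best-guess rate does not move.

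**Step 4: maximum imbalance in a stratum.** Half of the largest block: 6/2 = 3 with fixed sixes, 8/2 = 4 with the mix.

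**The case against.** The strongest reply is that certainty needs a great deal. One person must hold the complete, ordered allocation history of the next patient's stratum, for up to 12 strata, and know where each block begins. The document describes coach meetings as a place to discuss difficulties, not as an allocation log, and the list sits with an independent researcher. A reader might infer from the fixed block that recruiting researchers will in fact know one in four upcoming allocations. The document does not support that: it makes tracking possible and states nothing that prevents it, but does not say that it happens. One in four is also a ceiling for complete blocks.

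Discretion before allocation is limited too. Clinic staff do the first screening and referral. Eligibility is a numeric PHQ-9 range, and patients within it are to be invited. T0 is a scripted interview with questions read as printed, and the PHQ-9 score is a fixed sum of the participant's answers.

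Finally, biased selection needs only better-than-chance guessing, and varying the blocks does not reduce that.

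All of this stands as a limit on size. It does not remove the point. The hidden list blocks look-up but not deduction. A telephone interviewer still has some influence over whether a hesitant patient enters and how answers near a cut-off are recorded. Removing certainty is a real, if partial, gain.

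**Conclusion.** The point holds as an avoidable weakness in allocation concealment, not as an error or evidence of bias. Up to 25% of assignments, and about 21–22% under this trial's strata and sample size, could be deduced with certainty by someone tracking allocations by stratum.

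This assumes 1:1 blocks of exactly three and three, 12 strata, about 200 participants, and an observer with the full ordered history of the stratum. Several researchers or coaches each seeing only part of that history would lower the figure. The document does not say how far the history is shared.

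It would also be too much to infer that varying block sizes makes the sequence unpredictable. For an observer who knows the possible sizes, about 2.4% of assignments stay certain and about 66% can still be guessed. The benefit is real but modest, and worth taking because it costs almost nothing.

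**What to change.** Have the independent researcher regenerate the list with randomly varying block sizes, for example 4, 6 and 8, within the gender-by-center strata. Withhold the sizes from anyone who screens, obtains consent or interviews. The protocol need say only that sizes vary and are not disclosed to those roles.

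Cost: the list is computer generated and, according to Trial status, recruitment has not started, so the change is close to free. The one downside is a possible within-stratum imbalance of up to four instead of three.
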